### Sample size

A previous study learns that a correlation of 0.45 was found between Bispectral Index (BIS) monitoring and the Ramsay scale [35]. A similar correlation can be expected between the WAVcns and the VAS in the present study. However, in order to become a successful measure of sedation, we require the correlation between both measures to be significantly higher than 0.30. Although EEG monitoring would allow continuous data collection, the VAS will be completed only once or twice a day by relatives (more often by trained investigators) to keep burden as low as possible. As we expect patients can be monitored during 2–3 days on average, some 5 VAS scores (from relatives, more from staff) will be available per patient. This results in a close to 80% probability for our study to find a correlation higher than 0.30 if the actual correlation is 0.45.

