##### Aims of the study

To better understand how unconscious palliative sedated patients experience the last days of their life.To find out if they are really free of pain.To evaluate to what degree assessments of comfort based on behavioral observations are in line with the results from a brain function monitor and a ANI-monitor (analgesia nociception index).Additionally we want to find out if changes in the measured depth of sedation can be experienced by the patient, caregivers and relatives, especially in the last moments of life when sometimes unexpected changes have been measured.

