### Participants

In modal hospitals and modal homes for the elderly, forty patients will be selected. In each setting 20 participants will be included consecutively, which should result in 40 detailed case studies. Patients will be deliberately selected to gain maximum insight and reflect variability regarding medical conditions.

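### The 0.30 success criterion does not separate between-patient from within-patient correlation, and its stated power is reached only by pooling repeated scores as if independent

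*Protocol article*

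**What the plan says.** The Sample size section takes a correlation of 0.45 from an earlier study of another EEG index against a sedation scale and carries it over: "A similar correlation can be expected between the WAVcns and the VAS in the present study". The success rule follows: "in order to become a successful measure of sedation, we require the correlation between both measures to be significantly higher than 0.30". The power statement rests on repeated scores: "some 5 VAS scores (from relatives, more from staff) will be available per patient. This results in a close to 80% probability". The Participants section gives the number of patients: "In each setting 20 participants will be included consecutively, which should result in 40 detailed case studies".

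The section names no method for repeated measures, no alpha and no sidedness, and does not say which correlation is meant.

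The study asks two kinds of question. One is general correspondence between methods (third item in Aims of the study, second research question, first focus in Data-analysis). The other is change over time: the last aim is to "find out if changes in the measured depth of sedation can be experienced by the patient, caregivers and relatives", and the second focus in Data-analysis is detecting changes in comfort and awareness.

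**The concern.** With several scores per patient, a correlation over all pairs combines two things: whether patients with lower EEG values also receive lower ratings, and whether ratings move with the EEG value in the same patient. Only the second speaks to the aim on changes. If the single numerical rule is applied to the combination, neither a pass nor a failure shows whether raters notice a change. In addition, a power figure that counts repeated scores from one patient as independent is higher than this design delivers.

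**Working it through.** **Inputs.** Threshold 0.30, assumed correlation 0.45 and about 5 scores per patient (Sample size); 40 patients (Participants). ICCs are not given, so every ICC below is an assumption, taken as equal for WAVcns and VAS.

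**1. Reproducing the stated power.** Fisher z: atanh(0.45) − atanh(0.30) = 0.4847 − 0.3095 = 0.1752. Power = Φ(0.1752 × √(n − 3) − z).

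| Reading | n | One-sided 5% | Two-sided 5% |
|---|---|---|---|
| All pairs pooled as independent | 200 | 79.2% | 69.1% |
| One value per patient | 40 | 28.1% | 18.6% |
| Within-patient, 160 df | 161 | 71.1% | 59.6% |

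The bare probability that the observed correlation exceeds 0.30 is 99.3% at n = 200 and 85.7% at n = 40. Of the readings tried, only 200 pooled pairs tested one-sided at 5% matches the article.

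**2. What a pooled correlation measures.** With equal ICCs,

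pooled r = ICC × r_between + (1 − ICC) × r_within.

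Simulated success rates of the pooled one-sided 5% test against 0.30 (40 patients × 5 pairs, bivariate normal):

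| ICC | r_between | r_within | Pooled r | Pooled test succeeds | Within-patient test succeeds |
|---|---|---|---|---|---|
| 0.6 | 0.75 | 0 | 0.45 | about 68–70% | 0% |
| 0.4 | 0.75 | 0 | 0.30 | about 8–9% | 0% |
| 0.3 | 0.75 | 0 | 0.225 | about 1% | 0% |
| 0.6 | 0 | 0.45 | 0.18 | 2% | about 71% |
| 0.3 | 0 | 0.45 | 0.315 | 13% | about 72% |
| 0.6 | 0.45 | 0.45 | 0.45 | about 71% | about 72% |

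The last row matters too: if the two correlations are equal, the choice hardly affects the chance of success.

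**3. Error rate when clustering is ignored.** If both correlations equal 0.30, the variance of the pooled z is inflated by D = 1 + (5 − 1) × ICC², which is 1.36, 2.00 and 2.96 at ICC 0.3, 0.5 and 0.7. True rejection rate = 1 − Φ(1.645/√D):

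- ICC 0.3: 1 − Φ(1.411) = 7.9%
- ICC 0.5: 1 − Φ(1.163) = 12.2%
- ICC 0.7: 1 − Φ(0.956) = 17.0%

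Simulations gave 8–9%, 12–13% and 17–19%.

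**4. Power for the overall correlation with clustering allowed for.** If both correlations equal 0.45, the effective n = 200/D = 147, 100 and 67.6:

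- ICC 0.3: 0.1752 × √144 − 1.645 = 0.46, power 68%
- ICC 0.5: 0.1752 × √97 − 1.645 = 0.08, power 53%
- ICC 0.7: 0.1752 × √64.6 − 1.645 = −0.24, power 41%

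Simulation gave about 68%, 54% and 40%.

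**5. Power for the within-patient test** (one-sided 5%, true value 0.45, no serial correlation). Effective n = 40 × (m − 1) + 1 for m scores per patient.

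- m = 5: 0.1752 × √158 − 1.645 = 0.56, power 71%
- m = 3: 0.1752 × √78 − 1.645 = −0.10, power 46% (47% simulated)
- m = 5 shared by two relatives and centred per rater: 40 × 3 = 120 df, 0.1752 × √118 − 1.645 = 0.26, power about 60%

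Three scores is a realistic case. The article expects 2–3 days of monitoring with one or two ratings a day from relatives, which is 2 to 6 scores, so five lies near the upper end for them.

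**The case against.** The strongest reply is that correspondence between methods in general is a stated aim and comes before the aim on changes, and that settings can be compared only between patients. An overall correlation is therefore relevant. That stands, and it rules out simply replacing the target with the within-patient correlation. Centring also discards level: a monitor reading too high throughout in one patient could still pass, although the article interprets WAVcns by absolute range.

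A reader might infer that the test concerns mainly differences between patients. The documents do not support this. It needs an ICC above 0.5, none is given, and recording runs from the start of sedation until death, so variation within a patient may be large. A reader might also set the 68–70% against the nominal 5% as a false-positive rate. That is wrong: the pooled correlation in that scenario truly is 0.45, so rejecting is correct for that null. The fault there is the quantity targeted. The only genuine error inflation is that in step 3.

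Pooling is inferred from a power figure, and the analysis method may be set out in a plan that is not shown. That limits the claim about the analysis, but the printed power figure remains. Finally, this is an exploratory multi-case study whose coded events and qualitative work also address change, so the correlation is not the sole basis for conclusions. It is, however, the only rule with a number.

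**Conclusion.** The concern holds in limited form. The criterion leaves open which correlation must exceed 0.30, and its power is obtained only by treating about 200 repeated pairs from 40 patients as independent. A pooled result can inform general correspondence but cannot by itself answer the aim on changes. How misleading it would be depends on unknown ICCs: severe at ICC 0.6 if the two correlations differ, slight where they are equal. At ICC 0.3 a pass without tracking is rare, yet a failure despite good tracking remains likely if patient levels are unrelated.

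On the assumptions shown, the power is about 71% for the within-patient test at five scores and 46–47% at three, and about 68%, 54% and 40% for the overall correlation at ICC 0.3, 0.5 and 0.7, against the stated figure of close to 80%. These use a one-sided 5% level, which is itself inferred, and normal data. The 0.45 is not known to be a within-patient value. Strong serial correlation would disturb the within-patient test as well: with first-order autocorrelation of 0.8 in both measures, it rejected 10% of the time at a true 0.30.

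**What to change.** In the Sample size section, state which correlation is tested against 0.30, with alpha and sidedness. Estimate and report two correlations separately: within-patient (both measures centred on the patient's mean, within-patient degrees of freedom) and between-patient (patient means, n = 40). Use the within-patient one for the aim on changes. Keep the overall or between-patient one for general correspondence, with inference that allows for clustering by patient. A cluster-robust standard error alone would correct the precision but leave the two associations mixed. Restate the probability for each test, with the assumed ICCs and number of scores.

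This needs no new patients or data. The costs are a less favourable power figure, no contribution to the within-patient test from patients with a single score, and a further loss of degrees of freedom if centring is done per rater. The text should also say that 0.45 is an assumption for the within-patient correlation.

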### Procedures

For this prospective study methods from social sciences (qualitative data collection based on interviews, observation), quantitative assessments (scales to assess awareness and discomfort) and neurophysiological data will be combined. Hence, a combination of methods that can be considered fairly objective (e.g. EEG and physiological parameters) and rather subjective methods (e.g. observations by family members) will be used to assess discomfort and awareness. Therefore, the following data will be collected:

*1. Assessment by caregivers* (physicians and nurses) in the routine manner. As explained above, this can be based either on their ‘experience’ or on tools they routinely use in their practice. Every day all treating physicians and nurses will be asked to fill in a brief questionnaire (3 VAS scales) on the patient’s level of awareness (no awareness- completely aware), comfort (no pain – very severe pain) and ability to communicate (no communication possible - full communication possible). After the patient has deceased, all caregivers will be interviewed and asked to comment on their assessments.

*2. Family members’ perception* of the quality of the dying process, their opinion about the patient’s comfort and awareness and their impression of whether they had any kind of (non-verbal) contact with the patient. Parallel with the above described procedure, family members will also be asked to fill in the same 3 VAS scales. Semi-structured interviews will be conducted before and after the patient has deceased.

*3. Assessment by 2 trained investigators* using 1 scale that is mentioned in the Flemish palliative sedation guideline and 3 other scales that have been proposed in the literature [16]:3.1CCPOT (Critical Care Pain Observational Tool), a tool specifically developed for use in patients with limited consciousness [8].3.2RASS (Richmond Agitation-Sedation Scale) [21].3.3M-ESAS (Modified Edmonton Symptom Assessment Scale, validated for a Flemish Palliative Care Population) [22].3.4BPS-NI (Behavioral Pain Scale Non-Intubated) [23].

*4. Neurophysiological assessments* of distress and level of awareness using fMRI has been successfully used to detect awareness and distress that could not be detected by thorough behavioral assessment [10, 13, 14, 24, 25]. Issues of availability and extra stress incurred by patients when transferred are making the use of fMRI for practical and ethical reasons not feasible.

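### The stated power of nearly 80% matches a calculation that treats about 200 repeated scores on 40 patients as independent; allowing for clustering lowers it by an amount that depends on an unstated within-patient correlation

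*Protocol article*

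**What the plan says.** The Participants section sets the number of patients: "In modal hospitals and modal homes for the elderly, forty patients will be selected". The Sample size section takes its expected correlation from earlier work: "A previous study learns that a correlation of 0.45 was found between Bispectral Index (BIS) monitoring and the Ramsay scale". It then sets a hurdle: "we require the correlation between both measures to be significantly higher than 0.30".

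The amount of data is built up from duration and frequency. On duration, "we expect patients can be monitored during 2–3 days on average". On frequency, "the VAS will be completed only once or twice a day by relatives (more often by trained investigators". From these the section arrives at "some 5 VAS scores (from relatives, more from staff) will be available per patient", and the next sentence gives the power: "This results in a close to 80% probability for our study to find a correlation higher than 0.30 if the actual correlation is 0.45".

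The section gives no alpha, sidedness, total number of pairs, within-patient correlation or design effect.

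Procedures describes the VAS differently. Item 1 says "Every day all treating physicians and nurses will be asked to fill in a brief questionnaire (3 VAS scales", and item 2 has family members complete the same scales in parallel. Item 3 gives the trained investigators four other instruments (CCPOT, RASS, M-ESAS and BPS-NI) and no VAS.

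**The concern.** The section moves straight from scores per patient to power, so the number of scores carries the calculation. Scores from one patient over a few days share that patient's disease, drugs, brain and often the same raters. If both measures differ systematically between patients, 200 such pairs carry less information about the correlation than 200 pairs from 200 people.

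Two things are at stake. The design may have less power than stated to show the correlation that the section requires of a successful measure of sedation. And if the scores were later tested the way they appear to have been counted, the test would reject too often. The study is exploratory, but Research questions treats agreement with the EEG or ANI measurement as validation of an observational scale, so the threshold has consequences.

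**Working it through.** **Inputs from the protocol article.** 40 patients (Participants); about 5 scores per patient, null correlation 0.30, expected correlation 0.45, power close to 80% (Sample size). **Assumed, because not stated:** alpha 5%, sidedness, ICC.

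**Step 1: reproduce the stated figure.** For a Fisher-z test of one correlation against a non-zero null,

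power = Φ[(atanh 0.45 − atanh 0.30) × √(n − 3) − z].

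atanh 0.45 − atanh 0.30 = 0.4847 − 0.3095 = 0.1752. With n = 40 × 5 = 200, 0.1752 × √197 = 2.459.

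- One-sided 5%: Φ(2.459 − 1.645) = 79.2%. This matches.
- Two-sided 5%: Φ(2.459 − 1.960) = 69.1%. This does not.
- n = 40, one value per patient: 28.1% one-sided, 18.6% two-sided.
- Merely observing r above 0.30 with no test: 86% at n = 40, 99% at n = 200. Neither is near 80%.

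Exactly 80% needs about 205 pairs one-sided or about 259 two-sided.

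**Step 2: allow for clustering.** When the pooled correlation is estimated from m pairs per patient and both measures are clustered, the design effect is approximately DE = 1 + (m − 1) × ICCx × ICCy, and the effective number of pairs is 40m / DE. Take m = 5, equal ICCs, and equal within- and between-patient correlation:

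| ICC (both) | DE | Effective n | Power, one-sided 5% | Power, two-sided 5% |
|---|---|---|---|---|
| 0.1 | 1.04 | 192 | 78% | 67% |
| 0.2 | 1.16 | 172 | 74% | 63% |
| 0.3 | 1.36 | 147 | 68% | 56% |
| 0.5 | 2.00 | 100 | 53% | 41% |
| 0.7 | 2.96 | 68 | 41% | 29% |
| 0.9 | 4.24 | 47 | 32% | 21% |

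At ICC 1, DE = 5 and the effective n is 40, which gives the 28% floor.

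Simulation of 40 × 5 clustered bivariate normal pairs (20,000 runs, critical value corrected for size) gave 68%, 54%, 42% and 33% one-sided at ICC 0.3, 0.5, 0.7 and 0.9, in line with the table.

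A purely within-patient correlation has about 40 × 4 = 160 effective pairs and 71% power one-sided.

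**Step 3: add staff scores.** With the same formula, one-sided 5%:

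- ICC 0.3: m = 8 gives DE 1.63, effective n 196, power 79%; m = 10 gives DE 1.81, effective n 221, power 83%.
- ICC 0.5: m = 8 gives DE 2.75, effective n 116, power 59%; m = 10 gives DE 3.25, effective n 123, power 61%.

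**Step 4: size of a naive pooled test.** In the same simulation, a nominal one-sided 5% test that treats the 200 pairs as independent had a true size of about 8%, 13%, 17% and 22% at ICC 0.3, 0.5, 0.7 and 0.9.

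**The case against.** **The route to 80% is a reconstruction.** This stands. About 259 pairs tested two-sided would also give 80%, as would an effective n of about 150 at one-sided 10%. But the first also counts repeats as independent, and nothing in the text points to the second. A reader might infer that the figure can be reached in only one way; the document does not support that.

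**The ICC could be low.** This also stands. Recording starts on the day sedation begins, and the aims anticipate changes in its depth, so variation within a patient may be large. At ICC 0.1–0.2 power is 74–78%, close to the stated figure. A reader might infer that true power lies between 30% and 70%; that range leaves out low ICCs and the staff scores.

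**More scores are planned than five.** Sample size says staff will supply more, and Step 3 shows that this restores the figure at ICC 0.3 or below. It does not at 0.5 or above, and raters scoring at the same moment would share one EEG value.

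**The count of five is not contradicted by Procedures.** A reader might infer that daily scoring over 2–3 days yields only 2–3 scores per patient. That count is per rater: all treating physicians and nurses score daily, and so do family members. Even for one relative, five lies within the 2–6 implied by one or two scores a day for 2–3 days.

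**No pooled test is specified.** True. Data-analysis covers the qualitative and integrated work, and the correlation method may sit in an analysis plan that is not shown. The inflated error rate is therefore conditional, and at ICC 0.3 it is only about 1.6 times nominal (8% against 5%). An analysis plan could settle the method, but it would not make the printed power right.

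**Conclusion.** The point holds. From the inputs the section prints, its power follows from 200 independent pairs tested one-sided at 5%, and no allowance for repeated scores on 40 patients is visible. The size of the shortfall is not fixed by the document. With five scores per patient it runs from about 1 percentage point at ICC 0.1 (78% against 79%) to about 47 at ICC 0.9 (32%), through 68% at 0.3, about 54% at 0.5 and about 42% at 0.7. These figures assume a one-sided 5% test, equal ICC in both measures, and equal within- and between-patient correlation.

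The excess false-positive rate arises only if the pooled scores are tested as independent. Separately, Sample size and Procedures disagree on how often the VAS is scored and by whom.

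**What to change.** 1. Replace the power sentence in Sample size with power over a stated range of ICCs, giving alpha and sidedness. For example: with 40 patients and about 5 scores each, a one-sided 5% test of a correlation above 0.30 when the truth is 0.45 has about 78%, 68%, 54% and 42% power at ICC 0.1, 0.3, 0.5 and 0.7. Label the ICCs as assumptions.
2. Estimate and test the correlation with the patient as the cluster, by a patient-level bootstrap or a bivariate mixed model that reports within- and between-patient correlation separately.
3. Reconcile VAS scoring between Sample size (once or twice daily by relatives, more often by trained investigators) and Procedures (daily by caregivers and family, four other scales for investigators), and say which raters' scores enter the correlation.

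The cost is a rewording and one analysis method. The stated power becomes less favourable; no extra patients are needed.

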### Data-analysis

Analysis of qualitative data (interviews and video) will be done in accordance with the interpretative paradigm, aiming to understand meanings and actions and how people construct them, and follow the principles of Grounded Theory [36]. Coding of the neurological data will be performed by an experienced neurologist.

Video registrations will be coded in events and analysed using nVivo, a tool for qualitative analysis that enables researchers to code and analyze events and also allows importing and correlating video and neurophysiological data. A coding scheme will be developed to code behavioral signs of the patient, treatments (painful acts, medical acts, etc.) and environmental circumstances and changes (visits, noises…).

The involved researchers will intensively cooperate in the interpretation of the data. All data will be used for an overall assessment (using the transdisciplinary mixed methods case study approach) [37]. The analysis will focus on:comparison of the results based on the different methodsdetection of changes in level of comfort and awareness

The findings and interpretations will then be discussed in a multidisciplinary team consisting of members of the Mental Health and Wellbeing Research Group, the department of Anesthesiology and Perioperative Medicine, the department of Experimental Psychology (all from the Vrije Universiteit Brussel) and the Coma Science Group (University of Liège).

### Ethical aspects

Video/audio registration will only be made after explicit consent of the patient (if possible) and his next-of-kin.

The study protocol is approved by the biomedical ethics committee of the VUB/UZ Brussel (BUN 14320136504) and additional approval will be asked from participating hospitals. Written informed consent will be asked from the patient or his/her substitute decision maker.

We are aware that the data collection is challenging and delicate, especially because we will deal with dying patients and their family. Therefore, special attention will be given to clear communication about the aims of our study. We will explain participants that the study is not invasive and will not hinder the (sedated) patient and that the aim is to minimize the risk for suffering.

## Discussion

The objectives of the COMPAS study are to determine if more objective measures based on EEG and HRV are potentially useful in the assessment of comfort and pain during palliative sedation. To achieve these goals a transdisciplinary mixed methods multiple case study design is adopted, where both quantitative and qualitative data are being linked to neurophysiological data collected by monitoring devices. The methodological background of this particular type of mixed methods research has been described by Deschepper et al. in the paper *Linking numbers to perceptions and experiences: why we need transdisciplinary mixed-methods combining neurophysiological and qualitative data* [37]. Next to the already mentioned idiosyncratic aims the present study also aspires to be the first worked example of this methodological approach.

